# Efficacy and safety of thread embedding acupuncture for facial expression muscles atrophy after peripheral facial paralysis: study protocol for a randomized controlled trial

**DOI:** 10.1186/s13063-021-05696-6

**Published:** 2021-10-30

**Keywords:** facial expression muscles atrophy, peripheral facial paralysis, thread-embedding acupuncture, Randomized controlled trial

## Abstract

**Background:**

Facial expression muscles atrophy is one kind of sequelae after peripheral facial paralysis. It causes critical problems in facial appearance of patient as well as social and psychological problems. This study aims to evaluate the efficacy and safety of Thread-embedding acupuncture (TEA) for the management of facial expression muscles atrophy after peripheral facial paralysis.

**Methods:**

This is a patient-assessor blinded, randomized, sham-controlled trial. A total of fifty-six eligible patients will be randomly divided into TEA (n=28) and sham TEA (STEA) (n=28) groups. Both groups will receive TEA or STEA treatment at the frontal muscle and the depressor anguli oris muscle, at one predefined points once a week for eight weeks. Additionally, both groups will receive traditional acupuncture treatment at ten acupoints (GB20, LI4, LR3, GB12, ST7, SI18, LI20, BL2, SJ23, ST4) twice a week for eight weeks as a concurrent treatment. B-mode ultrasonography will be used to assess the changes in facial expression muscle thickness ratio of the affected/healthy side at baseline and at 10 weeks after screening, as the primary outcome. House-Brackmann Grade and lip mobility score will be measured and analyzed at baseline and 4, 8, 10, and 12 weeks after screening, as secondary outcomes.

**Discussion:**

The study will compare TEA with sham TEA to explore the feasibility for TEA in improving facial expression muscles atrophy after peripheral facial paralysis.

**Trial registration:**

Chinese Clinical Trial Registry, ChiCTR1900027170. Registered on 3 November 2019, http://www.chictr.org.cn/edit.aspx?pid=45173&htm=4

**Supplementary Information:**

The online version contains supplementary material available at 10.1186/s13063-021-05696-6.

## Background and rationale

Peripheral facial paralysis (PFP) is caused by peripheral neuronal lesions of the facial nerve, which can be either primary (Bell’s Palsy) or secondary [1]. PFP patients with level 3-5 injury can develop sequelae [2, 3] based on the Sunderland Classification system [4]. The PFP sequelae include synkinesis, contracture, spasm, crocodile tear syndrome, and facial expression muscles atrophy (FEMA) [5]. FEMA is easily ignored by patients and doctors since it occurs in the deep layer below the skin [5, 6]. However, an experienced doctor can diagnose FEMA at about three months after PFP onset [7]. Moreover, FEMA can persist for an extended period or permanently if not properly treated [5]. FEMA symptoms negatively impact the quality of life by causing psychological or social problems [8–10].

Studies have shown that acupuncture can prevent and alleviate muscular atrophy [11, 12], thus improving muscular functions [13, 14]. Thread-embedding acupuncture (TEA) is a novel subtype of acupuncture treatment that includes the insertion and embedding of certain absorbable medical threads, such as catgut, polydioxanone or polyglycolic acid among others, into subcutaneous tissues or muscles at specific points. Absorbable medical thread provides the function of traditional acupuncture for an extended period through the mechanical and chemical stimulations of the thread. It has been widely used for the treatment of musculoskeletal disease [15–17], obesity [18, 19] and cosmetic problems [20], especially in the reduction of facial wrinkles and improvement of skin elasticity in China and other Asian countries [21]. TEA has also been used for the treatment of PFP sequelae [22, 23].

However, the clinical efficacy of TEA for FEMA after PFP is unknown. TEA has been used for FEMA treatment after PFP in our hospital for many years. However, there is no evidence-based clinical research for this treatment. Many studies have assessed the safety and efficacy of TEA on facial connective tissues [15–21]. This study designed a patient-assessor blinded, randomized, sham-controlled trial to explore the efficacy and safety of TEA for the treatment of FEMA after PFP.

## Methods/design

### Objective

The aim of this study is to assess the efficacy and safety of TEA compared to sham TEA in alleviating FEMA after PFP.

### Study design

This is a patient-assessor blinded, randomized, sham-controlled efficacy trial on TEA for alleviating FEMA after PFP. A total of fifty-six eligible participants will be recruited from the inpatient and outpatient departments of the First Affiliated Hospital of Zhejiang Chinese Medical University. They will be assigned randomly into either the TEA or STEA group. Patients in both groups were given TEA (for TEA group), or STEA (for STEA group), and traditional acupuncture treatments (for both groups) for eight weeks. Regular follow-up will be conducted for up to four weeks after the intervention.

B-mode ultrasonography will be used to assess the changes in facial expression muscle thickness ratio of the affected/healthy side at baseline and 10 weeks after screening as the primary outcome. House-Brackmann Grade (H-B Grade) [24] and lip mobility score [25] will also be measured and analyzed at baseline and 4, 8, 10, and 12 weeks after screening, as secondary outcomes (Figs. 1, 2). The study protocol was approved by the Ethics Committee of the First Affiliated Hospital of Zhejiang Chinese Medical University on the Use of Human Subjects for Teaching and Research (approval No.2020-K-084–01) and registered in the Chinese Clinical Trial Registry (ChiCTR1900027170). The study design followed the Standard Protocol Items of Recommendations for Interventional Trials (SPIRIT) Checklist (Additional file 1).

**Fig. 1 Fig1:**
[figure not shown]
Flow chart for our randomized controlled trial on the efficacy and safety of TEA for FEMA after PFP

**Fig. 2 Fig2:**
[figure not shown]
Schedule of enrollment, interventions, and assessments

### Study subjects

#### Participants and setting

Patients with FEMA after PFP will be recruited. This study will be conducted in the First Affiliated Hospital of Zhejiang Chinese Medical University.

#### Inclusion criteria

Patients will be eligible for the study if they:
Male or female patients aged 18–65 years.Patients diagnosed with peripheral facial paralysis ≥3 months before screening.Patients with H-B Grade ≥III.Patients with atrophic facial expression muscles as revealed by B-mode ultrasonography. The muscle thickness of the affected side/healthy side ≤ 90%.

#### Exclusion criteria

Patients with central facial paralysis.Patients with bilateral facial nerve palsy or recurrent facial nerve palsy (more than two occurrences).Patients with a history of hypersensitivity to TEA or severe keloid.Patients with contraindications, such as skin diseases and hemostatic disorders (prothrombin time international normalized ratio [PT INR] >2.0 or taking anticoagulant) that inhibit TEA administration.Pregnant or nursing patients.Patients with serious acute or chronic organic diseases and systematic diseases.Patients with mental illness causing the inability to comply with the clinical trial protocol; or any other condition that can render the individual unsuitable for inclusion in the trial, as determined by the principal investigator.

### Elimination criteria

Patients included and did not meet the inclusion criteria.Patients who were not excluded and met the exclusion criteria.Eligible participants who are not on any clinical interventions.

### Dropout criteria

Poor compliance to the treatment (cannot finish 8-week treatment for personal reasons).Patients experiencing severe adverse events, complications, or special physiological changes.Voluntary dropout.

### Sample size

The sample size was based on previous similar studies [26], and advice from an expert group. The formula below was used to determine the sample size in each group (28 participants) (alpha (significance level), power (1-beta), dropout rate, and group sample ratio were 0.05, 0.90, 10%, and 1:1, respectively). σ indicates standard deviation (23.30) and d represents the mean difference between the two groups (21.54):
$$ \mathrm{n}=2{\sigma}^2{\left({\mathrm{Z}}_{\alpha /2}+{\mathrm{Z}}_{\beta}\right)}^2/{\mathrm{d}}^2 $$

### Recruitment

Subjects will be recruited through either of the following sources: (1) advertisements in newspapers and internet; patients who are interested can contact research staff by phone; or (2) the department of acupuncture and moxibustion of the First Affiliated Hospital of Zhejiang Chinese Medical University receives a high number of patients with FEMA after PFP. Recruitment advertisements will be released through posters and videos displayed on bulletin boards in the outpatient and inpatient lobbies of the First Affiliated Hospital of Zhejiang Chinese Medical University. If they are interested, they can contact research staff by phone. Informed consent will be obtained from eligible patients (Additional file 2).

### Allocation

After completing a baseline evaluation, eligible participants will be randomly assigned to either the intervention or the sham-controlled group in a 1:1 ratio by an independent investigator. Subjects in the intervention group will receive TEA treatment, whereas the subjects in the sham-controlled group will receive the sham treatment. Random numbers will be generated by a statistician from the Clinical Evaluation and Analysis Centre of The First Affiliated Hospital of Zhejiang Chinese Medical University using SPSS for Windows (Version 22.0; SPSS Inc., Armonk, NY, USA). Sealed opaque assignment envelopes were used for allocation concealment. Those envelopes will be stored in a locker and the key kept by the clinical research coordinator (CRC). CRC will offer the envelopes that correspond to the group allocation to the acupuncturist after completion of recruitment.

### Blinding

To achieve participant and evaluator blinding, the clinical research coordinator (CRC) will be the only one allowed to manage the allocation information as well as offer limited information to each researcher in accordance with their roles. The researchers involved in the study will be blinded to the allocation. In both TEA and STEA groups, the participants exhibited the same responses during the procedure. Throughout the whole treatment, the participants’ eyes will be covered with a blindfold to prevent them from observing the procedures. Data managers, statisticians, therapists, and interviewers will be independent and shall not be allowed to communicate allocations or other important information among each other.

The conditions for unblinding are: (1) if serious adverse events occur, and the participant has to be withdrawn from the trial, or (2) the end of the trial.

### Interventions

Specialists in the acupuncture & moxibustion department with at least three years of clinical experience and a license from the Ministry of Health of the People’s Republic of China will administer the treatments strictly following the detailed procedures. Any acupuncture or physiotherapy that can impact the results will be prohibited during the treatment and the follow-up period. Drugs prescribed for the participants four weeks before the trial will be allowed depending on their effect on outcomes. Information regarding medications administered to the participants will be recorded in the case report form (CRF).

### Standard operating procedures

#### Needle requirements

Disposable sterile TEA devices will be used in accordance with national standards within the validity period.

The TEA devices are covered with a protective cap before use and comprised of three parts: 0.7*30TWLB disposable hypodermic needle (Kangbao Medical Equipment co. LTD, Jiangsu, China), 0.4*50mm flat head acupuncture needle (Jiachen Acupuncture Medical Equipment co. LTD, Jiangsu, China) and a 1.0-cm absorbable thread (4-0’, Polyglycolic acid thread made by B. Braun Surgical, S.A, Rubi, Spain) (Fig. 3). The absorbable thread is a major TEA component and is internally buried in the treatment areas. The flat head acupuncture needle is used to push the thread out of the injection needle head into the body tissue.

**Fig. 3 Fig3:**
[figure not shown]
Parts of a thread-embedding acupuncture device

#### Hygiene of the operator

The operator will be required to sterilize his or her hands using a sanitizer and wear sterile gloves and mask before the TEA and STEA procedures. For the acupuncture procedures, the operator will be required to sterilize his or her hands with a sanitizer before operation.

#### Sterilization of the operation points

The skin on the operation points (5 cm diameter from the acupoint as the center) will be sterilized twice using a cotton swab dipped in 0.45%–0.55% povidone-iodine.

### Procedure

#### TEA group

Participants in this group will receive TEA treatment at two predefined points once a week for eight weeks. Point selection and details of this procedure were based on a consensus of clinical experts and modified from those used in previous study [22].
Selection of points: Point 1 is located in the frontal (FRO) muscle. Point 1 is in the middle of the line between the eyebrows and the front hairline, forming a straight line from the pupil to the front hairline. Point 2 is located in the depressor anguli oris (DAO) muscle. Point 2 is 1 cm below the oral angle of the line, forming a vertical line to the mandibular margin through the oral angle (Fig. 4).Detailed procedures: After covering the patient’s eyes and sterilizing the skin, practitioners will perform the intervention procedure. The injection needle with thread will be transversely inserted along the line downward from 1 cm above point 1 or 2 in the layer where the two target muscles are. The handle of the flat head acupuncture needle will be pushed to insert the thread in the target muscle after which the injection needle and the flat head acupuncture needle will be removed. Sterile cotton balls will be used to press local pinholes to prevent bleeding.

**Fig. 4 Fig4:**
[figure not shown]
Location of the two operation points

#### STEA group

Participants in this group will receive STEA treatment at two predefined points (same as TEA group) once a week for eight weeks. Patients in the STEA group will undergo the same procedure as those in the TEA group except that there will be no thread in the TEA device.

Communication will be minimized during interventions to prevent bias except where necessary.

### Concurrent treatment

In China acupuncture has been historically used to treat sequelae after facial paralysis. And research has showed that acupuncture treatment was effective in improving sequelae of facial paralysis [13, 26]. It is highly accepted by most of the patients. So traditional acupuncture will be used as a concurrent treatment for both groups twice a week for eight weeks to improve adherence to the intervention. Moreover, acupuncture treatment will be performed immediately after TEA or STEA treatments. A 0.25*40mm disposable acupuncture needle (Jiachen Acupuncture Medical Equipment co. LTD, Jiangsu, China) will be inserted to a depth of 5 mm and retained for 30min in the following 10 acupoints (Table 1): GB20, LI4, LR3, GB12, ST7, SI18, LI20, BL2, SJ23, ST4.

**Table 1 Tab1:** Location of the acupoints

Acupoint (standard abbreviation/Chinese nomenclature)	Location
GB20/Fengchi (Affected side)	In the anterior region of the neck, inferior to the occipital bone, in the depression between the origins of sternocleidomastoid and the trapezius muscles
LI4/Hegu (Bilateral Extremity)	on the highest point of the fleshy joining between the index and thumb fingers when they are stretched outwards
LR3/Taichong (Bilateral Extremity)	In the depression anterior to the junction of the first and second metatarsal bones
GB12/Wangu (Affected side)	In the posterior and inferior depression of the mastoid process behind the ear
ST7/Xiaguan (Affected side)	On the face, anterior to the ear, in the depression between the zygomatic arch and the condyloid process of the mandible
SI18/Quanliao (Affected side)	In the lower margin depression of zygomatic bone
LI20/Yingxiang (Affected side)	Next to the ala of the nose
BL2/Cuanzhu (Affected side)	On the medial end of the eyebrow
SJ23/Sizukong (Affected side)	In the depression of the tail of the eyebrow
ST4/Dicang (Affected side)	Outside the corner of the mouth, just below the pupil

### Treatment period

All participants will receive TEA or STEA treatment once a week and concurrent acupuncture treatment twice a week for eight weeks. One of the two acupuncture treatments will be given on the same day and another one will be administered 2-3 days after the first one.

### Criteria for discontinuing interventions

Treatment will be ended if participants meet any of the following conditions:

1. Patient had serious adverse events during or after treatment.

2. Patient was misdiagnosed after randomization.

3. Patient found to be pregnant after randomization.

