### Data monitoring and trial steering committee

A data monitoring committee (DMC) with members from the Clinical Evaluation and Analysis Centre of The First Affiliated Hospital of Zhejiang Chinese Medical University regularly meet to monitor the study data. The DMC will monitor the overall quality and integrity of the data, examine the original CRFs, interview the researchers, verify the record of adverse events, perform an interim analysis, and confirm that the study conforms to the principles of this protocol. A Data and Safety Monitoring Board (DSMB) was also set up to monitor the performance and safety of the trial, which is composed of 5 experts from different fields of the First Affiliated Hospital of Zhejiang Chinese Medical University to ensure the safety of this trial every 6 months. The DMC and DSMB are independent of the trial researchers and have no competing interests. DSMB will reveal a participant’s allocated intervention and make the final decision on whether to terminate the trial. The First Affiliated Hospital of Zhejiang Chinese Medical University will verify participant enrolment, consent, and costs.

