### Systemic reactions

Dizziness or fainting during or after treatment.

Systemic allergy.

Systemic infection.

For patients with common adverse reactions, appropriate medical care will be given to ease local bleeding, bruising and so on.

Severe AEs are defined as symptoms or diseases that result in hospitalization or prolonged hospitalization, disability, a life-threatening situation or even death. In this trial, systemic infection and allergy are two major severe AEs. Severe AEs will be reported to the Ethics Committee within 24 hours. The Ethics Committee will provide medical suggestions for the research team and decide on whether the patient should continue with the ongoing treatment. Proper compensation will be given to cover their medical costs.

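### After a serious adverse event, two sections end treatment or class the patient as a dropout outright, while a third leaves continuation to the Ethics Committee

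*Protocol article*

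**What the plan says.** Four sections of the protocol article bear on what follows a serious or severe adverse event.

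- **Criteria for discontinuing interventions:** "Treatment will be ended if participants meet any of the following conditions". The first condition is "Patient had serious adverse events during or after treatment". No discretion is given and no decision-maker is named.
- **Dropout criteria:** the list includes "Patients experiencing severe adverse events, complications, or special physiological changes", again without condition.
- **Systemic reactions:** "Severe AEs are defined as symptoms or diseases that result in hospitalization or prolonged hospitalization, disability, a life-threatening situation or even death". Such events go to the Ethics Committee, which will give medical advice and "decide on whether the patient should continue with the ongoing treatment".
- **Blinding:** one of the two unblinding conditions is "if serious adverse events occur, and the participant has to be withdrawn from the trial".

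The article defines severe events once, under Systemic reactions, and does not define serious events separately. The Adverse events section adds that the need for withdrawal is recorded for each event.

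**The concern.** Site staff must act on these rules as soon as an event happens. One section tells them that treatment stops, another that the patient is a dropout, and a third that a committee will decide whether treatment goes on. Following one of them can breach another.

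Two further matters depend on the answer. Unblinding after an event requires that the participant must be withdrawn, so unclear withdrawal makes unblinding unclear too. The primary outcome is measured only at baseline and week 10. If a patient is treated as a dropout before week 10 and not scanned, the only post-baseline value is missing, and last observation carried forward (LOCF) puts the baseline value in its place.

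**Working it through.** **1. Do the sections describe the same event?** Dropout criteria and Systemic reactions both say *severe*, so that comparison needs no assumption about terms. Criteria for discontinuing interventions says *serious*. The definition of severe under Systemic reactions consists of seriousness criteria (hospital admission, disability, threat to life, death), and no other definition is offered. The natural reading is that both words cover the same event.

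**2. Can the rules be followed together?** Take a patient with such an event during the eight treatment weeks.

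| Section | Committee decides against continuation | Committee allows continuation |
|---|---|---|
| Criteria for discontinuing interventions (treatment ends) | followed | breached |
| Dropout criteria (patient is a dropout) | followed | breached |
| Systemic reactions (Committee decides) | followed | followed |
| Blinding (unblind if withdrawal is necessary) | condition can be met | cannot be settled: it depends on whether the patient counts as withdrawn |

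The conflict is therefore conditional. It appears whenever the Committee uses its stated power to allow continuation. If it can never do so, that power is empty.

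**3. What happens to the data?** The full analysis set contains everyone randomized and treated at least once, so a treated patient stays in it either way. What can change is the week-10 value. A patient scanned at week 10 contributes an observed change. A patient not scanned has the baseline carried forward, so the change is 0. An event after the week-10 scan costs no primary data.

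**4. How large could this be?** First, the planned sample size. Inputs from the Sample size section: σ = 23.30, d = 21.54, two-sided α = 0.05, power 0.90, dropout 10%.

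- n = 2σ²(1.960 + 1.282)²/d² = 24.59, rounded up to 25.
- 25/0.90 = 27.8, rounded up to 28 per group. The stated figure is reproduced.

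Now suppose that k of the 28 patients in the thread-embedding arm lose their whole effect through LOCF. The expected difference becomes 21.54 × (1 − k/28). Power is Φ(difference/(σ√(2/28)) − 1.960), with σ√(2/28) = 6.227.

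| k | Expected difference | Power at 28 per arm |
|---|---|---|
| 0 | 21.54 | 93.3% |
| 1 | 20.77 | 91.6% |
| 2 | 20.00 | 89.5% |
| 3 | 19.23 | 87.0% |

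The values of k are assumptions, since the article gives no event rate. The table also assumes no average change in the sham arm, no such losses there, and an unchanged SD. It uses the comparison of means behind the sample size formula.

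**The case against.** The strongest reply is that little of this is truly contradictory. Ending treatment and being classed as a dropout are compatible. The Blinding section says when unblinding is allowed, not who is withdrawn. If the Committee decides against continuation, all four sections are satisfied. All of that stands, and it limits the point to two sections against a third, in the case where continuation is allowed. The Adverse events section, which records the need for withdrawal event by event, might support reading the dropout list as possible reasons rather than automatic ones. Even so, the discontinuation section says outright that treatment ends, and the clash with the Committee's power remains.

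A reader might infer several stronger things that the documents do not support:

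- **That the four sections can never be followed together.** They can, as the table shows.
- **That an intense event without hospital admission falls into a gap between severe and serious.** Only one definition is given, and it rests on seriousness. The two words are loose terminology more than two concepts.
- **That any allergy triggers the rules.** The sentence naming allergy follows the definition and sits under Systemic reactions; local allergy is listed elsewhere. It reads most naturally as giving the main examples.
- **That patients would be analysed under different rules.** One full analysis set and one imputation rule apply. Only the availability of the week-10 value may differ.
- **That handling would differ between arms because the thread causes more events.** This is conceivable, but the article gives no figure.

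A condensed article may also leave follow-up after stopping treatment to the full protocol. Its absence is not the finding. The finding is that the rules that are printed conflict.

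**Conclusion.** The point holds in limited form. The discontinuation and dropout sections state outcomes without condition, and Systemic reactions reserves the treatment decision to the Ethics Committee. Once the Committee allows a patient to continue, the text cannot be followed as written, and the unblinding condition rests on a withdrawal status that the text leaves open. The clash between Dropout criteria and Systemic reactions rests on one shared word. The clash with the discontinuation section rests on reading *serious* as *severe* in the defined sense, which is the only definition available.

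The statistical effect is probably small. Under the stated assumptions, one or two affected patients in the active arm would leave power at 91.6% or 89.5%, close to the planned 90%. The reason to act is consistent handling of a safety event in a trial that, according to Trial status, was already recruiting, with ten patients under treatment. It should be corrected, but it does not undermine the design.

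**What to change.** Reconcile Dropout criteria, Criteria for discontinuing interventions and Systemic reactions, and align Blinding with them:

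1. Use one term throughout, with the definition already given under Systemic reactions.
2. State once whether treatment ends automatically or by decision, and who decides. Which clinical rule applies is for the sponsor and the Ethics Committee to settle.
3. State one trigger for unblinding that matches that rule.
4. Distinguish stopping treatment from leaving the trial, so that a patient who stops treatment and still consents has the week-10 ultrasound instead of a carried-forward baseline.

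The cost is a wording amendment, with the formal application that the Modification of the protocol section requires. No patients or new procedures are added, since the week-10 scan is already scheduled.
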